### Safety considerations

We do not anticipate any serious safety concerns arising from this largely behavioural intervention. The use of the videofluoroscopy as part of the intervention is sometimes associated with aspiration of barium contrast material but barium pneumonitis is reported to be rare at <1%.^47^ The additional radiation exposure associated with the procedure is roughly the equivalent of 2 months of background radiation that an adult in the UK may experience from the environment, and considered minor in the context of the patient's overall treatment. The procedure will be undertaken by an experienced SLT familiar with the protocol for dealing with an adverse event related to barium inhalation. The procedure is also a well-established part of routine clinical practice.

### Data collection and management

We devised a number of study specific forms including a case report form (CRF), screening log, enrolment log, training log for any study-related training and file note entry forms for any relevant ad hoc communication. Patient names will be replaced by a study number on all study forms and completion of CRFs will be in accordance with GCP guidelines. A site file containing all relevant documents as stipulated by local research and development and governance guidelines will be maintained throughout the study and securely stored in a locked cabinet. All patient-reported questionnaires will also be securely filed. Non-identifiable quantitative data will be transferred from the questionnaires and CRFs to a specifically designed Microsoft Access database by a data manager. The database will first be tested using mock data to ensure that it meets the requirements for data entry. A random check of ∼10% of the data inputted will be reviewed against the original source by the researcher (RG) to estimate an error rate. This information will help ensure that a robust data management plan is in place for a more formal trial. The researcher will maintain an electronic diary of relevant information pertaining to the study processes on a password-protected laptop computer.

### Analysis

We will use mainly descriptive analysis and summary statistics to address our aims. Study screening and enrolment logs will be used in determining the rate of recruitment into the study. All qualitative information (researcher diary), minutes of study-related discussions and meetings will be imported into NVIVO 10, a software database to facilitate the organisation and thematic coding of qualitative or textual data. The researcher is in a unique position of being embedded within the clinical team, and therefore able to make observations over the duration of the study in a naturalistic manner. This approach to process analysis arguably may provide more useful information than the use of post hoc focus groups and interviews that rely on participant memory and may be removed from context.^48^ Observing and collecting information in this way also means that the researcher can observe the interplay of other factors (eg, multiple studies competing for the same patient group, prevailing views of the treating consultant about the value of the proposed intervention and how busy the clinic is) that may reveal vital information about the barriers and facilitators to recruitment.

We will also report on the practicality of implementing the protocol, for example, obtaining timeslots for videofluoroscopy; average time taken for the recruitment and consent process; utility of the chosen randomisation method and suitability of the study-specific forms including the CRF. This information will be used to optimise components of the protocol and study process in preparation for a larger trial.

As a range of outcome measures will be collected, we will look at the suitability of each measure, the ease of collection and the quality and completeness of the data collection. We will observe the relationships (concordance and discordance) between the different outcome measures to help inform the most suitable choice of primary and secondary measures for a definitive trial. Important parameters such as SD and estimates of effect size will be used to inform the sample size calculation. Based on the available literature, we will aim to specify the target difference (clinically meaningful difference) for the chosen primary outcome. The primary outcome measure will be chosen from potential candidate measures on the basis that it is valid, practical and feasible to obtain and has expert agreement (RCSLT clinical expert group) that it reflects a good summary measure to answer the question of whether the new intervention is effective in improving swallowing.

Patient acceptability to participation and randomisation will be determined using a previously developed questionnaire.^49^ Self-reported adherence to the intervention will be explored via a brief study questionnaire. Previous studies reported that full adherence to exercises during radiotherapy was under 15%.^27^
^30^ In a Danish study of a similar intervention to the current study, an average of 35% of patients reported doing their exercises at least once a day between 1 month and 11 months after treatment.^22^ We have therefore selected 35% as the minimum target adherence for our study.

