### Study population, setting and recruitment plan

The study will take place at a single NHS hospital site (Head and Neck Cancer Centre) with a catchment population of 1.5 million. The study sample will be drawn from the population of patients with newly diagnosed HNC referred to the cancer centre, and discussed at the weekly multidisciplinary team (MDT) meeting. Potential patients for the study (based on diagnosis) will be identified during the meeting by the researcher (RG), research nurse or other members of the MDT. The research team will ensure that the treating consultant is aware of potentially eligible patients so that he/she may introduce the study during the consultation with the patient if appropriate. For this feasibility study, sample size was determined pragmatically using the general guidance suggested by Lancaster and colleagues^39^ who recommend that n of 30 is sufficient to estimate key parameters in a feasibility study. Based on a conservative annual referral of ∼70 newly diagnosed stage III and stage IV patients with HNC to the Head and Neck Centre, we estimated that it will take about 9 months to recruit a total of 32 patients to this study based on recruiting 60% of eligible patients. Eligibility criteria for inclusion in the study are listed in box 1.
Box 1Inclusion and Exclusion CriteriaInclusion:
Patients with newly diagnosed stage III and stage IV head and neck cancer.Discussed at the head and neck MDT and planned for treatment via surgery and/or chemoradiotherapy or combinations thereof.Able to provide informed consent.Proficiency in English satisfactory to participate/engage in the intervention.Aged 18 and above.Exclusion:
Patients with previous head and neck cancer treatment.Patients who are mid treatment or those receiving palliation.Patients who are to be treated solely by non-standard treatment that is not surgery, radiotherapy, chemoradiotherapy or combinations thereof. Patients treated by chemotherapy, brachytherapy and photodynamic therapy alone will be ineligible.Patients who are planned for a total laryngectomy.Patients who are considered vulnerable or unable to provide informed consent.Patients with brain tumours and other primary sites not within head and neck.

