### Randomisation and allocation

Eligible patients will be randomly assigned in a 1:1 ratio between usual care and intervention groups (figure 3 for trial flow chart). Patients will be stratified by first-line treatment; surgery or chemoradiation, a known factor that impacts swallowing outcomes.^13^ It will therefore be necessary to ensure a balance of primary treatment modality across the groups. Owing to the small numbers in this study, random block permutations will be employed to ensure a close match in numbers in the intervention and usual care groups at any given point during the trial.

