### Interventions and procedures

*Usual care group*: This group will receive the usual pretreatment care offered by the SLT prior to their upcoming surgery and/or chemoradiation. The SLT clinical team consisting of four members participated in a series of consensus meetings regarding the delivery of usual care to facilitate equipoise. All four team members involved in the delivery of usual care have also undergone good clinical practice (GCP) training. A usual care manual was written and agreed by the SLT clinical team prior to initiation of the study to ensure a level of consistency among the clinicians. Usual care pretreatment is one 45 min consultation as described below:
General case history taking and introduction of SLT role.Clinical baseline screening of swallowing and communication function. This is usually based on an oro-motor assessment; 100 mL water swallow test;^40^ a clinician-rated Performance Status Scale indicating the normalcy of diet texture and public eating score;^41^ and a clinician-rated scale for chewing, communication and swallowing.^42^ Maximal jaw opening using a TheraBite measure and voice quality ratings using the GRBAS (Grade of Hoarseness, Roughness, Breathiness, Asthenia, Strain) rating scale are also recorded.The patient is provided with a general overview of the planned treatment (surgery or chemoradiation) and information about the likely side effects such as mucositis and taste changes and impact of treatment on swallowing and communication function.General advice and exercises are offered to patients planned for chemoradiation at this appointment. Patients are provided with a general exercise sheet that includes instructions for eight different swallowing exercises, for example, passive jaw stretches. This is included as part of the information pack given to all patients receiving radiotherapy. Patients are advised that it *may* be helpful to start doing the exercises before treatment.

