Patients will undergo a radiological assessment of their swallow function in the fluoroscopy suite at the hospital site. This procedure is part of the SIP SMART intervention informing the selection of targeted exercises, and is used as part of patient education. A standard protocol for this clinical procedure will be adopted for the study.^35^ The patient will be asked to swallow a variety of food textures; fluoroscopic images of the lateral and anterior–posterior plane captured at a rate of 30 frames per second will be recorded on a swallow workstation (Digital Kay Pentax Swallow workstation, USA). This will be available for later analysis of swallow physiology. The fluoroscopy screening time is usually 2–3 min.Patients will subsequently be shown a video animation (Dysphagia App, Northern Speech Services, USA) to explain the basic mechanics of swallowing and to orientate them to key structures such as the tongue, base of tongue, airway and oesophagus. Patients will thereafter be shown their own videofluoroscopy and helped to identify the key structures using this newly acquired knowledge. The clinician will encourage the patient to provide commentary and or ask questions as they watch their own swallowing.The videofluoroscopy assessment will be used to tailor the information, advice and exercises given to the patient during the pretreatment session and to facilitate discussion about the rationale for exercises and possible consequences of not doing exercises.Further detail about the intervention content and behavioural strategies used is provided in the SIP SMART manual. This is not included in this paper, but can be requested from the first author.

Patients in both groups will follow the usual care pathway for SLT rehabilitation post treatment (see figure 3 for trial flow chart). The number of SLT rehabilitation sessions for all patients will be recorded. Patients will be informed that exercises may be amended post treatment based on updated swallowing assessment.

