### Criteria for success

This study will be viewed as feasible to proceed to a definitive trial if:
a suitable outcome measure is determined, and sample size estimated;recruitment rate into the trial reaches an average of four patients a month;patients report generally positive views about participation and acceptance to randomisation as determined by questionnaire evaluation;patients in the intervention group are more adherent than those in usual care, with at least 35% of intervention group patients reporting satisfactory to good adherence to exercises.

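### The between-arm half of the adherence success criterion rests only on open self-report, so over-reporting in the coached arm could meet it without a true difference

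*Protocol article*

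**What the plan says.** **Measure.** The Analysis section states: "Self-reported adherence to the intervention will be explored via a brief study questionnaire". The section on baseline and follow-up outcome measures describes two questions made for this trial, one on percentage adherence and one free-text question on reasons. Table 1 lists a self-reported adherence item at 1, 3 and 6 months. The article names no diary, device or observed record as a source for the criterion.

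**Rule.** The fourth item under Criteria for success has two clauses. Intervention patients must be more adherent than usual-care patients, with no margin given, "with at least 35% of intervention group patients reporting satisfactory to good adherence to exercises". The Analysis section takes the 35% from a study in which patients reported their own exercising.

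**What each arm hears.** Under Interventions and procedures, the intervention arm's videofluoroscopy is used to tailor advice and "to facilitate discussion about the rationale for exercises and possible consequences of not doing exercises". In usual care, patients planned for chemoradiation receive general advice and a sheet of eight exercises, and are advised that it may "be helpful to start doing the exercises before treatment".

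**Who knows and who handles the data.** Patients and staff know the allocation (Randomisation and allocation). One clinician, who is also the study researcher, delivers the whole package. Under Data collection and management, forms carry study numbers, a data manager transfers the data, and the researcher reviews about 10% of entries against the original source.

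**The concern.** A between-arm comparison of self-reports measures behaviour plus any difference in willingness to report well. Here that willingness may well differ. Patients know their arm, and one arm has had a personal discussion of why to exercise and what may follow from not doing so, with the person running the study. The clause has no margin, so any observed excess meets it. A difference in reporting would then be read as evidence that the package changes behaviour, and would count towards proceeding to a definitive trial. The Discussion names the lack of blinding and explains how bias in the videofluoroscopy ratings is limited, but does not link unblinding to adherence.

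**Working it through.** **The plan's own figure.** The article plans on this basis: "Based on a conservative annual referral of ∼70 newly diagnosed stage III and stage IV patients", "based on recruiting 60% of eligible patients". That gives 70 × 0.60 / 12 = 3.5 patients a month, and 32 / 3.5 = 9.1 months, which reproduces "we estimated that it will take about 9 months to recruit a total of 32 patients". With 1:1 allocation ("Eligible patients will be randomly assigned in a 1:1 ratio between usual care and intervention groups") there are 32 / 2 = 16 per arm.

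**The rule in counts.** 0.35 × 16 = 5.6, so at least 6 of 16 intervention patients must report satisfactory to good adherence. I take more adherent to mean a higher proportion reporting this; the article does not spell it out.

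**Formula.** Let X ~ Bin(16, a) be the reported count in the intervention arm and Y ~ Bin(16, b) the count in usual care. The chance of meeting both clauses is P(X ≥ 6 and X > Y), summed exactly. The chance of meeting the between-arm clause alone is P(X > Y). True adherence is set equal in the two arms. The true levels and the over-reporting are assumptions.

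| True adherence, both arms | Reported, intervention (a) | Reported, usual care (b) | P(X > Y) | Both clauses |
|---|---|---|---|---|
| 25% | 25% | 25% | 41.9% | 16.4% |
| 25% | 35% | 25% | 66.7% | 45.7% |
| 25% | 40% | 25% | 76.8% | 61.4% |
| 35% | 35% | 35% | 42.7% | 34.3% |
| 35% | 45% | 40% | 54.4% | 52.1% |
| 35% | 45% | 35% | 65.7% | 61.5% |
| 35% | 50% | 35% | 75.5% | 73.2% |

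**Equal over-reporting, for comparison.** If both arms over-report by 10 points, the chance of meeting both clauses is 34.3% from a true 25% and 41.8% from a true 35%. Splitting the rise on that basis:

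- From 25%: 34.3 − 16.4 = 17.9 points come from the general lift across the 35% line, and 45.7 − 34.3 = 11.4 points from the difference between arms.
- From 35%: 41.8 − 34.3 = 7.5 points come from the lift, and 61.5 − 41.8 = 19.7 points from the difference.

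The between-arm clause taken alone hardly moves under equal over-reporting (41.9% to 42.7%, and 42.7% to 43.0%). It moves by 23 to 25 points when only one arm over-reports by 10.

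**Loss to follow-up.** With 12 per arm answering, the threshold is 5 of 12. From a true 25%, the chance of meeting both clauses goes from 13.9% to 37.7% with 10 points of one-sided over-reporting, and to 51.5% with 15. The pattern is the same.

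**The case against.** Several counter-arguments have weight.

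- **The 35% clause compares like with like.** It speaks of patients reporting adherence, and its benchmark was also reported by patients, so some over-reporting is already in the threshold. This stands, and it confines the main weakness to the between-arm clause.
- **Adherence cannot carry the decision.** A reader might infer that over-reporting alone could send the project to a definitive trial. The document does not support that: a suitable outcome measure with a sample size, four patients a month, and generally positive views on participation and randomisation are also required.
- **The contrast between arms is easily overdrawn.** The article does not say that intervention patients are told they must exercise. The hedge in usual care concerns starting before treatment, not whether exercises help at all. Both arms then follow the same usual rehabilitation pathway, and the questions are asked after treatment. An asymmetry remains, since only one arm's description includes the consequences of not exercising, but it is one of degree.
- **Data handling is not unprotected.** A reader might infer that nothing separates the answers from the treating researcher. Study numbers and a data manager are already in place; the access the article states is the source check of about 10%. Who hands out and collects the forms may be in the full protocol, and the article's silence on it is no fault.
- **The scenarios are chosen.** One-sided over-reporting is the unfavourable case; with 5 points in usual care the 61.5% falls to 52.1%. The 34.3% with no over-reporting comes from small numbers and the absent margin, not from self-report. In the 35% scenarios the absolute target is truly met.

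None of this protects the between-arm clause, which has no self-reported benchmark to absorb a difference in reporting.

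**Conclusion.** The point holds for the between-arm clause. It rests only on unblinded self-report, in a design that gives the two arms different reasons to report well, and it is used as a pass/fail condition. One-sided over-reporting of 10 points would raise the chance of meeting both adherence clauses, with no true difference, from 16% to 46% at 25% true adherence and from 34% to 62% at 35% (52% if usual care over-reports by 5 points). These figures assume 16 answering per arm, independent patients and the stated amounts of over-reporting, none of which the article estimates. They show that a false pass on this criterion can occur, not that it will. The 35% clause is affected less, and a pass here is a pass on one of four criteria.

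**What to change.** 1. Have patients in both arms return the adherence questions under study number directly to the data manager. Use the same sentence on both forms: neither their therapist nor the researcher will see individual answers.
2. Under Data collection and management, assign the source check of these items to someone other than the person who delivers the package. Otherwise that assurance would be untrue for the sampled forms.
3. Under Criteria for success, keep the 35% clause and make the between-arm comparison descriptive, reported as open self-report, rather than a pass/fail condition. A sentence saying that adherence alone cannot support proceeding would add nothing, because the four criteria already apply jointly.

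The cost is a return route, one sentence on the form, a reassigned check and a short edit to the criteria; the data manager already handles these data. The researcher could no longer chase unclear answers directly. Some self-report bias would remain, since confidential return does not remove recall error or the effect of coaching on patients who know their arm.

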### Criteria for success

This study will be viewed as feasible to proceed to a definitive trial if:
a suitable outcome measure is determined, and sample size estimated;recruitment rate into the trial reaches an average of four patients a month;patients report generally positive views about participation and acceptance to randomisation as determined by questionnaire evaluation;patients in the intervention group are more adherent than those in usual care, with at least 35% of intervention group patients reporting satisfactory to good adherence to exercises.

## Discussion

To the best of our knowledge, this is the first randomised UK study of a behavioural swallowing exercise intervention for patients with HNC registered on the trials database. By undertaking a feasibility study and identifying key uncertainties, any future study may be optimised to make best use of resources.^50^ This study follows earlier work on intervention development bringing together expertise from different fields including clinical dysphagia management and behaviour change. It benefits from the use of newer paradigms in health research including the use of consultative and consensus meetings to devise a treatment manual to specify the content of *usual care*, a common omission when reporting such interventions.^51^ It is likely to provide a rich source of information about how readily patients with a new diagnosis of HNC will accept and participate in a self-management-type intervention. It will also provide a preliminary indication of the recruitment potential for rehabilitation therapy trials for this population. A recent UK study^52^ that randomised HNC patients to either a pretreatment gastrostomy tube or a nasogastric tube reported recruiting only 23% of eligible patients, highlighting the importance of this feasibility work. It is well known that the treatment of HNC involves a complex care pathway with multiple disciplines being involved, particularly at the pretreatment stage. The feasibility of undertaking a clinical trial at this point in the patient pathway is compounded by the challenges of approaching patients to participate in a trial shortly after receiving a cancer diagnosis. Insights from this study may therefore have more widespread relevance for future studies of this population.

Limitations of the study include the inability to blind participants and staff to the randomisation allocation as all patients in the intervention group will receive a videofluoroscopy as part of the intervention. Based on the limited number of individuals trained in rating videofluoroscopies using the MBS impairment profile, the same SLTs involved in usual care delivery will be rating the assessments. For this reason, we have chosen to use a consensus rating from three clinicians as this method is likely to introduce the least bias. We have not planned to evaluate fidelity in delivering the intervention at this stage, as only one individual will be delivering the intervention (RG). In a larger trial, training will be required by all clinicians before delivering the intervention and fidelity checks will be built into the research process. In spite of these limitations, the current study represents a first and important step towards examining the feasibility of undertaking a full-scale RCT within NHS hospitals to determine the effectiveness of a pretreatment swallowing intervention for patients with HNC, delivered by SLTs.

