## Methods and analysis

### Study design

This study forms the preliminary testing phase described within the MRC complex interventions framework. Following on from our development work, we will conduct a two-arm parallel group non-blinded randomised controlled feasibility study. The SPIRIT^38^ (Standard Protocol Items for Randomised Interventional Trials) checklist of was used to inform the content of this protocol.

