**Figure 3 BMJOPEN2016014167F3:**
[figure not shown]
Trial flow chart.

Patients will be allocated to one of two groups using an online computer-generated randomisation service provided by an external company: http://www.sealedenvelope.com/. The company is registered with the Information Commissioners Office (ICO) and inspected by the MHRA (UK trials regulator). Following consent, the researcher or research nurse will enter the password-protected website and complete relevant information regarding first-line treatment. Randomisation is immediate, and the group allocation is emailed within a few minutes. This process is undertaken in the presence of the patient after signed consent is obtained, ensuring that the allocation is concealed until this point and simultaneously made known to the patient and researcher. Allocation is not blinded as the patient and staff will be aware that the new intervention includes a baseline videofluoroscopy or X-ray of swallowing. Patients allocated to the usual care group are advised that they will be sent an appointment in the post to see an SLT prior to their treatment as per the usual care pathway. Patients allocated to the intervention group are given an appointment and a further information leaflet on having a videofluoroscopy to assess how well the muscles and nerves function when swallowing different textures of food and drink. All patients are given three questionnaires to complete and return prior to their appointment with the SLT.

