At 6 months, a videofluoroscopy will be conducted on all patients using the standardised Modified Barium Swallow Impairment Profile Protocol (MBS Imp Profile), and analysis.^35^ Three SLT clinicians who have completed a 25 hour online training module and obtained the minimum 80% reliability score will provide consensus ratings for these assessments. Standard assessment rating forms developed as part of the MBS Imp Profile will be used to score the videofluoroscopies. We will also rate aspiration from the videofluoroscopies, based on the widely used 8-point Penetration-Aspiration Scale (PAS).^46^

As we anticipate that adherence to swallowing exercises should be associated with better swallowing, we will also collect intermediate outcomes on adherence using two simple questions developed for this trial. The questions will ask about percentage adherence over a specified time, and a free text question to gather further information about any specific reasons for adherence/non-adherence to exercises.

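### The 6-month videofluoroscopies are rated by the usual-care therapists with no masking described, and three-rater consensus does not reduce a bias that the raters share

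*Protocol article*

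**What the plan says.** All references are to the protocol article.

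- *Study design* calls the trial a "two-arm parallel group non-blinded randomised controlled feasibility study".
- *Randomisation and allocation* (text after the flow chart) gives the reason: "Allocation is not blinded as the patient and staff will be aware that the new intervention includes a baseline videofluoroscopy". The limitations in the *Discussion* repeat the "inability to blind participants and staff to the randomisation allocation".
- *Baseline and follow-up outcome measures* gives every patient a videofluoroscopy at 6 months under one standardised protocol. Three trained SLTs "will provide consensus ratings for these assessments", covering the MBS impairment profile (MBSImP) and the Penetration-Aspiration Scale (PAS).
- The *Discussion* explains that few people are trained to rate, so "the same SLTs involved in usual care delivery will be rating the assessments". It continues: "For this reason, we have chosen to use a consensus rating from three clinicians as this method is likely to introduce the least bias".
- *Interventions and procedures* puts the usual-care team at four SLTs, has one clinician deliver the new intervention, and sends both arms through the same SLT rehabilitation after treatment.
- *Data collection and management* replaces names with study numbers on study forms. It does not mention the recordings given to raters.

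**The concern.** The article identifies a source of bias, namely raters who deliver one of the two arms, and answers it with a device suited to a different problem. Consensus helps when raters err independently. It does not help when they hold the same expectation about an arm, and discussion can pass one rater's knowledge of a patient's allocation to the other two.

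At stake is the usefulness of MBSImP and PAS, the only instrumental swallowing scores in Table 1. The aims include examining concordance between measures, choosing a primary outcome for the definitive trial and informing its sample size. *Analysis* says that SDs and effect-size estimates will feed that calculation, and *Criteria for success* makes a suitable outcome and an estimated sample size a condition for proceeding.

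**Working it through.** The article states no figure on this point, so there is none to reproduce. The check has four steps.

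**1. Does the reason for not blinding apply to the 6-month reading?** The reason is the baseline videofluoroscopy in the intervention arm. At 6 months both arms have the same examination, so having it does not identify the arm. The shortage of trained raters explains who rates. It does not explain why they would have to rate with the arm known.

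**2. How likely is it that raters know the arm?** The three raters come from the four-person usual-care team, and a different clinician delivers the intervention. A rater who remembers a patient's pretreatment consultation can therefore infer usual care. If the four SLTs share these consultations evenly (an assumption) and 16 of the 32 planned patients are controls, about 16 × 3/4 = 12 controls will have been seen before treatment by one of the raters. Shared rehabilitation after treatment adds further contact in both arms.

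**3. What does consensus do to a shared bias?** Take rating = truth + b (shared, present in one arm) + independent rater error. The document gives no values, so these are assumed: true SD 1, rater-error SD 0.5, b = 0.3, no true effect, 16 per arm.

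- Expected false difference: b = 0.30 with one rater. With three raters it is (b + b + b)/3 = 0.30.
- Rater-error SD: 0.50 with one rater, and 0.50/√3 = 0.29 for a mean of three. A simulation using the median of three as a stand-in for consensus gave 0.335, with mean differences of 0.298 (one rater) and 0.301 (three).
- SE of the arm difference = √(1 + 0.25/k) × √(2/16), treating consensus as a mean of k raters: 0.395 for k = 1 and 0.368 for k = 3.

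The false standardised difference, b/√(1 + 0.25/k), over a range of b:

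| Assumed b | One rater | Three raters |
|---|---|---|
| 0.2 | 0.18 | 0.19 |
| 0.3 | 0.27 | 0.29 |
| 0.5 | 0.45 | 0.48 |

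The noise falls and the bias stays, so in standardised terms the bias grows slightly.

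**4. What could follow for the definitive trial?** Suppose one of these scores became the primary outcome and its observed effect set the sample size. With n per arm = 2(1.96 + 0.8416)²/d² (80% power, two-sided 5%), a true effect of 0.5 SD needs 15.70/0.25, or 63 per arm.

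| Assumed error in d | d used | n per arm | Power at true 0.5 |
|---|---|---|---|
| +0.2 | 0.7 | 33 | 53% |
| +0.3 | 0.8 | 25 | 42% |
| +0.5 | 1.0 | 16 | 29% |
| −0.2 | 0.3 | 175 | above 80% (oversized) |

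The last row is there because the direction of bias is unknown: 15.70/0.09 = 174.4, rounded up. These are worked examples, not estimates for this trial.

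**The case against.** The case on the other side is substantial, and most of it limits the weight of the point.

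- **A reader might infer that raters are shown identified recordings.** The document does not say so. It describes no masking, calls staff blinding impossible and offers only consensus, so unmasked reading is the likely meaning. File coding could still sit in a fuller protocol.
- **A reader might infer that individual scores are discarded.** The article promises consensus ratings and does not exclude independent scoring first. Inter-rater agreement is also not a listed aim.
- **A reader might take the sentence about keeping fluoroscopic images for later analysis as proof that the 6-month recordings are stored and read afterwards.** That sentence concerns the baseline examination in the intervention arm. Later reading at 6 months is plausible, given three raters and standard scoring forms, but it is not stated.
- **The authors do not claim that consensus removes bias.** They disclose the overlap and say only that "this method is likely to introduce the least bias". Raters also complete 25 hours of training, must reach at least 80% reliability and use a standardised protocol. This stands as mitigation of random error and scoring drift. It does not address shared knowledge of the arm.
- **This is a feasibility study.** The analysis is largely descriptive, no efficacy test rests on these scores, and the target difference is to come from the literature. The primary outcome will be chosen on validity, practicality and expert agreement, from candidates that include MDADI and FACT-HN. This stands and narrows the harm.
- **Masking would leak.** At one site with four SLTs and about 32 patients, some will be recognised. This also stands, but incomplete masking is still better than none.

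**Conclusion.** The point holds as a recommended, inexpensive improvement to a limitation that the authors disclose. The raters deliver usual care, staff are not blinded, no masking of raters is described, and the one stated safeguard does not act on a bias the raters share. The common 6-month examination means that nothing stated in the article prevents masked reading.

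The harm is confined to three uses of MBSImP and PAS as candidate outcomes: their effect-size estimate, their concordance with other measures, and the judgement of their suitability. Its size and direction cannot be derived from the document. The figures above rest on assumed SDs and shifts and show only that consensus leaves b unchanged. A reader might conclude that the feasibility findings as a whole are compromised or that the trial cannot proceed without this change. The document does not support that: recruitment, acceptability and adherence do not depend on these ratings, and no success criterion uses a between-arm videofluoroscopy contrast.

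**What to change.** Before 6-month rating begins, add to *Baseline and follow-up outcome measures*:

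1. Existing staff outside the rating group, such as the data manager or research nurse, give each 6-month recording a code, remove name, date and arm, and place the recordings in random order across arms. No baseline videofluoroscopy is shown beside them.
2. Each of the three trained SLTs records independent MBSImP and PAS scores, and the three then agree a consensus score.
3. Agreement between the independent scores is reported.
4. Raters note any recording where they recognised the patient, and the number is reported by arm.

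In the *Discussion*, say that consensus limits independent rater error and that coded, randomly ordered reading is the safeguard against knowledge of the arm.

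The cost is some file-handling time and an extra set of scores per recording. No new rater or procedure is needed. Masking will be incomplete, because the four-person team also sees patients in rehabilitation after treatment. The count of recognised patients shows how incomplete it was, which is useful for planning the definitive trial.
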